## Effect predictors

Presence of DSM-IV Axis I mood/anxiety disorders is assessed by the SCID-I (First et al. 2012) which is a structured clinical interview. The interviewer rates answers on standardized questions during the interview on a scoring form. Subsequently, the presence or absence of symptoms is assessed. The SCID-I is administered by trained interviewers. An experienced psychiatrist (EBI) supervises the administration of the SCID-I. In the current study, neuroticism is assessed with the NEO Five Factor Inventory (Costa and McCrae 1992). A shorter version of the Revised NEO Personality Inventory (NEO-PI-R), the NEO-FFI has 60 items (12 per domain) derived from the original 240 items. The five factor domains assessed by this measure are neuroticism, extraversion, openness to experience, agreeableness, and conscientiousness. The psychometric properties of the Dutch NEO-FFI are good (Hoekstra et al. 1996).

## Process measures

*Mindfulness skills* are assessed with the 24-item Five Facet Mindfulness Questionnaire Short Form (FFMQ-SF). The FFMQ consists of five subscales: observing, describing, acting with awareness, non-judging of inner experience and non-reactivity to inner experience. The FFMQ is sensitive to change in mindfulness-based interventions (e.g. (Gu et al. 2015)). A Dutch 24-item short form of the FFMQ (FFMQ-SF) was developed and assessed in a sample of 376 adults with clinically relevant symptoms of depression and anxiety and cross-validated in an independent sample of patients with fibromyalgia (Bohlmeijer et al. 2011). The FFMQ-SF was positively related to well-being and openness to experience and inversely related to measures of psychological symptoms, experiential avoidance, and neuroticism.

In addition, in both group and internet-based MBCT the following process measures are administered at the start of each weekly session in order to determine processes of change during both interventions. In the group MBCT they are handed out in paper by the teacher, in the internet-based MBCT intervention they are provided online at the beginning of a new training week. The Mindful Attention Awareness Scale (MAAS; (Brown and Ryan 2003)) is administered weekly to assess *mindful attention in daily life*. The MAAS has been shown to have an similar factor structure in cancer patients as in the general population (Carlson and Brown 2005). Chronbach’s alpha for the Dutch version ranged between .82 and .87 (Schroevers et al. 2008). Positive and negative affect is assessed weekly using the International Positive and Negative Affect Scale - Short Form I-PANAS-SF). The crosscultural factorial invariance, internal reliability, temporal stability, and convergent and criterion-related validities of the I-PANAS-SF were found to be acceptable (Thompson 2007).

*Working alliance* is measured with a translated and shortened form of the Working Alliance Inventory (WAI; (Horvath and Greenberg 1989)), consisting of three subscales assessing: 1) how closely client and therapist agree on and are mutually engaged in the goals of treatment, 2) how closely client and therapist agree on how to reach the treatment goals, and 3) the degree of mutual trust, acceptance, and confidence between client and therapist. Patients score on a 5-point scale ranging from rarely to always (Stinckens et al. 2009; Hatcher and Gillaspy 2006). The 12-item inventory was validated in a Dutch-speaking sample and a recent study showed that internal consistency of the short form was > .80 for all separate subscales and .87 for the total (Janse et al. 2014). The WAI is administered before session 2, 5 and 9.

Self-reported *group cohesion* is assessed in the group MBCT condition with the Dutch Group Cohesion Questionnaire (GCQ) that has been used in cancer patients before (May et al. 2008). The GCQ consists of four subscales: the bond with the group as whole, the bond with other members, cooperation within the group and the instrumental value of the group bond. Each item is rated from 1 (totally disagree) to 6 (totally agree). Internal consistency of all scales was reported to range from adequate to good (0.66–0.88) (Trijsburg et al. 2004). The GCQ is administered before session 2, 5 and 9.

*Adherence* is assessed during the entire treatment period with a calendar (both for group and internet-based MBCT) on which participants fill out whether they adhere to both formal (e.g. the sitting meditation) and informal (e.g. 3-min breathing space) mindfulness exercises. Adherence to protocol has been shown to mediate the effects of MBCT on depressive symptoms [72].

### Semi-structured interviews

In order to more fully understand how interventions bring about change, it is important to complement quantitative research with qualitative research (Shennan et al. 2011). For this reason participants’ views on barriers and facilitators of the internet-based MBCT are explored in more detail by conducting semi-structured interviews in a purposive sample of participants in the trial.

### Statistical analysis

#### Sample size

Based on post treatment HADS scores within the routine outcome data of cancer patients who received mindfulness at the Helen Dowling Institute, we expected post treatment HADS scores of 10.6 (SD 6.4) in the MBCT interventions and 14.8 (SD 8.1) in the TAU condition. In the power calculation we ignored the dependency caused by the therapy groups, which has been found in previous research to be small (Van Aalderen et al. 2012). As we compare both group and internet-based MBCT to TAU, we corrected the corresponding alpha level to 0.025. Assuming a power of 0.9, a sample size of 65 per condition is needed. Taking an estimated expected dropout rate of 15 % in the group MBCT and TAU and 30 % in the internet-based MBCT into account, we aim to recruit 76 participants in the group MBCT and TAU conditions and 93 in the internet-based MBCT, thus 245 patients in total.

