#### Statistical analysis

All analyses are carried out using the intention to treat and per protocol samples. The primary analysis is aimed at showing superiority of group MBCT and internet-based MBCT compared to TAU in terms of psychological distress directly post treatment in the intention to treat sample. Secondary analyses of the stability of the treatment effect are conducted using the data from the assessments at 3 and 9 months post-treatment, using linear mixed models to control for possible dependency caused by the repeated measurements.

We will use the bootstrapping procedure as it provides the most powerful and reasonable method of obtaining confidence limits for specific indirect effects under most conditions (Preacher and Hayes 2008). In all mediation analyses, post-treatment HADS scores are controlled for baseline HADS scores. Residual change scores for all potential mediators are calculated (MacKinnon 2008). To explore whether the mediators (partly) affect the relation of condition on post-treatment symptom levels, the model including the potential mediators is compared with the model without mediators for both univariate and multivariate models. Subsequently, 95 % bias corrected and accelerated confidence intervals (95 % CI) (Efron 1987) are calculated to explore the contribution of each individual mediator and the group of mediators in total.

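### The only level given for the two MBCT-versus-TAU contrasts is 0.025 each; stating a Holm step-down would raise the chance of showing both formats superior, with no extra patients

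*Protocol article*

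**What the plan says.** The protocol article, under Sample size, sets the level used for the two comparisons with TAU: "As we compare both group and internet-based MBCT to TAU, we corrected the corresponding alpha level to 0.025". The same paragraph gives the expected outcomes, "we expected post treatment HADS scores of 10.6 (SD 6.4) in the MBCT interventions and 14.8 (SD 8.1) in the TAU condition", and the resulting size, "Assuming a power of 0.9, a sample size of 65 per condition is needed". It then allows for dropout and arrives at 245 patients: "we aim to recruit 76 participants in the group MBCT and TAU conditions and 93 in the internet-based MBCT".

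Under the following heading, Statistical analysis, the article states the aim: "The primary analysis is aimed at showing superiority of group MBCT and internet-based MBCT compared to TAU", on distress directly after treatment in the intention-to-treat sample. That section gives no significance level, no sidedness and no procedure for handling the two contrasts together. The 0.025 in the sample-size paragraph is therefore the only level the article attaches to them.

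**The concern.** The primary aim covers both formats, so the outcome of most interest is that each beats TAU. Suppose 0.025 is carried unchanged into the final analysis, and one contrast gives p = 0.01 and the other p = 0.04. The second format is then declared not superior. Holm would declare both superior and still hold the family-wise error at 0.05. What is at stake is the conclusion on the second format, whichever that is, when its p-value falls between 0.025 and 0.05 and the first format has already succeeded.

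**Working it through.** **Inputs (Sample size paragraph).** Means 10.6 and 14.8, so the difference is 4.2. SDs are 6.4 and 8.1, giving a root-mean-square SD of √((6.4² + 8.1²)/2) = √53.285 = 7.30 and a standardised difference of 4.2/7.30 = 0.575. There are 65 analysed per arm, the TAU arm is shared, and patients are treated as independent, as in the article's own calculation.

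**Reproducing the article's 65.** n per arm = 2(z₁ + z₂)²·SD²/Δ², with SD²/Δ² = 53.285/17.64 = 3.021 and z₂ = 1.282 for power 0.9.
- One-sided 0.025 (numerically the same as two-sided 0.05): 2 × (1.960 + 1.282)² × 3.021 = 63.5, so 64. The t-based version gives 65, with power 0.902. This reproduces the stated figure.
- Two-sided 0.025: 2 × (2.241 + 1.282)² × 3.021 = 75.0, so 75. The t-based version gives 77. With 65 per arm, power is 0.851 (normal) or 0.843 (t).
- Dropout: 65/0.85 = 76.5 (stated 76) and 65/0.70 = 92.9, so 93. The total is 76 + 76 + 93 = 245.

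Because sidedness is not stated, both readings are carried forward.

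**The two rules.** Fixed level: reject each contrast if its p ≤ 0.025. Holm: reject the smaller p if it is ≤ 0.025 and, only then, reject the larger if it is ≤ 0.05. The first step is the same, so the chance of at least one rejection is identical and no rejection is lost. The rules differ only when one p is ≤ 0.025 and the other lies between 0.025 and 0.05.

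**Why Holm keeps the error rate.** If both nulls are true, an error requires the smaller p to be ≤ 0.025, which has probability at most 2 × 0.025 = 0.05. If one null is true, a false rejection requires its own p to be ≤ 0.05.

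**Size of the gain.** One million simulated trials per scenario, t tests:

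| Quantity | One-sided: fixed → Holm | Two-sided: fixed → Holm |
|---|---|---|
| Both effects 4.2: power, group contrast | 0.9024 → 0.9335 | 0.8428 → 0.8815 |
| Both effects 4.2: power, internet contrast | 0.9028 → 0.9338 | 0.8429 → 0.8815 |
| Both effects 4.2: both contrasts won | 0.8439 → 0.9061 | 0.7593 → 0.8367 |
| Both effects 4.2: at least one won | 0.9612, unchanged | 0.9263, unchanged |
| No effect in either: any false rejection | 0.0434, unchanged | 0.0449, unchanged |
| Only group works: false rejection for internet | 0.0253 → 0.0505 | 0.0252 → 0.0425 |

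The gain in winning both is 0.9061 − 0.8439 = 0.062 (one-sided) or 0.8367 − 0.7593 = 0.077 (two-sided). That is also the share of trials in which the two rules disagree. Half of it falls to each contrast: 0.031 or 0.039. No fixed-level rejection was lost in any simulated trial. The simulated 0.0505 is the theoretical limit of 0.05 apart from simulation error, √(0.05 × 0.95/1,000,000) ≈ 0.0002, and a t reference that is only approximate when SDs differ.

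**The case against.** The strongest reply is that the 0.025 is a planning level, not a decision rule. It stands in the sample-size paragraph, and the article names neither Bonferroni nor single-step testing. A team intending Holm could well size each contrast at 0.025, because that is Holm's first step. The analysis plan is not shown and may already contain a step-down. This stands. A reader might infer that the protocol has committed itself to a single-step test, but the text does not say so, and its silence on the procedure is not in itself a fault.

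The second reply is that a fixed 0.025 is a valid choice with simple matching intervals. This also stands, so the point concerns efficiency only.

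Three further inferences should be resisted.
- That the stricter level protects against nothing. If only group MBCT works, it keeps the false-positive rate for internet MBCT at 0.025 instead of 0.043 to 0.05.
- That true effects are thrown away in general. The chance of at least one success does not change.
- That the shared TAU arm argues for Holm. Neither rule uses that correlation, and with no effect in either arm their error rates are identical.

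Nor do the documents single out internet MBCT as the contrast that would lose. They expect the same mean of 10.6 for both formats and state the aim for both. A larger gain under a weaker internet effect would rest on an assumption from outside the article.

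**Conclusion.** The point holds as a conditional and modest one. If 0.025 is applied to each contrast in the final analysis, Holm at a family-wise 0.05 is at least as powerful in every case. It adds about 3 to 4 percentage points per contrast and 6 to 8 points for showing both formats superior. The family-wise error stays within 0.05, although the error for a single ineffective format can rise to that limit.

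The figures assume the article's means and SDs, 65 analysed per arm, equal effects in the two formats, and no clustering by therapy group. The one-sided column is the reading that reproduces 65. On the two-sided reading the stated power of 0.9 is not reached under the fixed level (0.84 to 0.85). That is a separate and larger matter, which Holm does not repair, since its per-contrast power is still 0.88. This is a cheap improvement, not an error in the plan.

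**What to change.** In the Statistical analysis section, state the decision rule for the two primary contrasts: the one with the smaller p-value is tested at 0.025 and, if it is significant, the other at 0.05. State whether the tests are one- or two-sided. Fix this before outcome data are analysed. If the full analysis plan already contains such a rule, the article needs only to agree with it.

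Keep 0.025 as the sizing level and leave the recruitment targets of 76, 76 and 93 unchanged. The cost is one sentence. Intervals that match Holm exactly are less simple, so report 97.5% intervals alongside (one-sided bounds if the tests are one-sided). Say that the decision follows the step-down p-values, because a second contrast significant only at 0.05 will have a 97.5% interval that includes zero. The authors should also accept openly that the second contrast, once reached, carries a false-positive risk of up to 0.05 instead of 0.025.

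### 65 per arm gives 90% power at alpha 0.025 only if the tests are one-sided, which the protocol does not state; two-sided, power is about 84% per comparison

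*Protocol article*

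**What the plan says.** The Sample size section of the protocol article gives all inputs but one. For the effect, "we expected post treatment HADS scores of 10.6 (SD 6.4) in the MBCT interventions and 14.8 (SD 8.1) in the TAU condition". For multiplicity and the result, "we corrected the corresponding alpha level to 0.025. Assuming a power of 0.9, a sample size of 65 per condition is needed"; the reason given for the correction is that both MBCT formats are compared with TAU. The same section sets therapy-group clustering aside ("In the power calculation we ignored the dependency caused by the therapy groups") and inflates for a "dropout rate of 15 % in the group MBCT and TAU and 30 % in the internet-based MBCT", which leads to 76 + 76 + 93 = 245 recruited.

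The missing input is whether 0.025 is one-sided or two-sided. The Statistical analysis section gives only the objective: "The primary analysis is aimed at showing superiority of group MBCT and internet-based MBCT compared to TAU".

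**The concern.** An alpha of 0.05 cut to 0.025 for two comparisons is ordinarily read as two-sided. On that reading the stated alpha, power and sample size do not fit together: 65 per arm is too few for 90% power at 0.025.

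The primary analysis is at stake. On the two-sided reading, the type II error for each comparison with TAU is about 16% rather than 10%. A non-significant result in one MBCT arm would then be taken as stronger evidence against that format than the design supports.

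**Working it through.** **Inputs, all from the Sample size section.** Difference 14.8 − 10.6 = 4.2. Variances 6.4² + 8.1² = 40.96 + 65.61 = 106.57. Root-mean-square SD √(106.57/2) = 7.30, so d = 4.2/7.30 = 0.575. Power 0.90. Two comparisons share one TAU arm. There is no clustering and no baseline adjustment.

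**Formula (normal approximation).** n per arm = (z_α + z_β)² × 106.57 / 4.2² = (z_α + z_β)² × 6.041, with z_β = 1.282.

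**Reproducing the plan's 65.** For one-sided 0.025, z_α = 1.960 and n = 10.507 × 6.041 = 63.5, so 64. The t-test version (noncentral t, unequal variances) has power 0.898 at 64 and 0.902 at 65. So 65 is the smallest n that reaches 0.90. Two-sided 0.05 has the same z_α and gives the same result.

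**Two-sided 0.025.** Here z_α = 2.241 and n = 12.411 × 6.041 = 75.0.

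| Test | n, normal | n, t-test | Power at 65 (t) |
|---|---|---|---|
| One-sided 0.025 (same cutoff as two-sided 0.05) | 64 | 65 | 0.902 |
| Two-sided 0.025 | 75 | 77 | 0.842 |

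At 65 per arm and two-sided 0.025, the difference detectable with 90% power is 4.56 points.

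**Recruitment at 77 evaluable per arm.** 77/0.85 = 90.6, so 91 each for group MBCT and TAU. 77/0.70 = 110 for internet-based MBCT. The total is 91 + 91 + 110 = 292, against 245 stated.

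**Both comparisons together.** Simulated three-arm trials with 65 per arm and the shared TAU arm, two-sided tests, family-wise 5%:

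| Procedure | Per comparison | Both |
|---|---|---|
| Bonferroni (0.025 each) | 0.84 | 0.76 |
| Holm (smaller p at 0.025, then the other at 0.05) | 0.88 | 0.84 |

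**Family-wise error at the cutoff that reproduces 65.** Simulated under no effect in either arm, using that cutoff in both directions gives a family-wise error of about 8.5% to 8.7%. Counting only errors in favour of MBCT gives about 4.2%.

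**Baseline adjustment (an assumption; the article gives no correlation).** Adjusting for baseline HADS multiplies the SD by √(1 − r²). At 65 per arm and two-sided 0.025, power is about 86% at r = 0.2, 88% at r = 0.3, 90% at r = 0.4 and 93% at r = 0.5.

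**The case against.** The strongest reply is that the stated figures are consistent as they stand. A one-sided family-wise 0.05, halved for two comparisons, gives 0.025 per test. With the article's means and SDs, that gives exactly 65 per arm for 90% power. The aim is directional, sidedness is not stated, and an article may leave it to the full protocol or the SAP. On this reading the correction does enter the number, since an uncorrected one-sided 0.05 would need only 53 per arm by the t-test.

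Much of this stands. A reader might infer that the calculation was run at an uncorrected two-sided 0.05, that the correction was claimed but never applied, and that the stated power is simply wrong. The document does not support that. One-sided 0.025 and two-sided 0.05 share a critical value, so the arithmetic cannot show which was used.

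The reply does not settle the matter. Superiority names an objective and is routinely tested two-sided, and nothing in the article declares one-sided tests. The one-sided reading also needs a starting level of one-sided 0.05, which is lenient and undeclared. Each test would then be no stricter than an unadjusted two-sided 0.05. Nor is this only a detail left to another document: alpha, power and n are all fixed here, and whether they agree depends on the missing word.

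It can also be said that Bonferroni is valid and that Holm is a preference. That is true. Holm is offered because it is never less powerful and controls the same error rate.

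**Conclusion.** The point holds in conditional form. The stated 65 per arm and 90% power agree with alpha 0.025 only under one-sided testing. Under the usual two-sided reading, power is about 6 percentage points lower per comparison (84% against 90%) and 12 more patients per arm would be needed (77 against 65).

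These figures rest on the article's own means and SDs, equal arms of 65 evaluable patients, an analysis without baseline adjustment, and no clustering. A reader might also infer that baseline adjustment closes the gap anyway. It does so only if the baseline to post-treatment correlation is roughly 0.4 or more, and the article gives no value.

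Severity is moderate: effect estimates and the stated per-test alpha are untouched, and the remedy is mainly wording.

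**What to change.** 1. Keep the recruitment target of 245. State that the two comparisons of MBCT with TAU are two-sided at a family-wise 5%, and restate the power at 65 per arm as about 84% per comparison, for an unadjusted analysis with therapy-group clustering ignored.
2. If one-sided testing was intended, keep the 90% but declare the one-sided family-wise 0.05 explicitly.
3. With two-sided tests, replace plain Bonferroni with Holm. This raises power to about 88% per comparison and 84% for both.
4. If baseline HADS adjustment is cited as a further gain, give the assumed correlation with a range, and note that 90% at 65 per arm needs roughly 0.4.

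The cost is a corrected sample-size paragraph and one sentence on Holm. No extra patients are needed. The drawback is a less favourable stated power.

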#### Statistical analysis

All analyses are carried out using the intention to treat and per protocol samples. The primary analysis is aimed at showing superiority of group MBCT and internet-based MBCT compared to TAU in terms of psychological distress directly post treatment in the intention to treat sample. Secondary analyses of the stability of the treatment effect are conducted using the data from the assessments at 3 and 9 months post-treatment, using linear mixed models to control for possible dependency caused by the repeated measurements.

We will use the bootstrapping procedure as it provides the most powerful and reasonable method of obtaining confidence limits for specific indirect effects under most conditions (Preacher and Hayes 2008). In all mediation analyses, post-treatment HADS scores are controlled for baseline HADS scores. Residual change scores for all potential mediators are calculated (MacKinnon 2008). To explore whether the mediators (partly) affect the relation of condition on post-treatment symptom levels, the model including the potential mediators is compared with the model without mediators for both univariate and multivariate models. Subsequently, 95 % bias corrected and accelerated confidence intervals (95 % CI) (Efron 1987) are calculated to explore the contribution of each individual mediator and the group of mediators in total.

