Thus, it is unknown whether internet-based MBCT has similar effectiveness as group-based MBCT in alleviating distress in cancer. Therefore, we primarily compare post-treatment psychological distress between group-based and internet-based MBCT. Also, effectiveness in reducing psychological distress up to nine months post-treatment will be compared between group- and internet-based MBCT. Moreover, we would like to determine whether the two interventions could reduce fear of cancer recurrence and rumination. Also, at the other end of the psychological spectrum, both group- and internet-based MBCT might be able to improve positive mental health in cancer patients compared to TAU. Furthermore, alongside the clinical trial, cost-effectiveness of both MBCT interventions compared to TAU will be determined. We expect both interventions to be cost-effective compared to TAU.

We do not expect all individuals to benefit similarly from the two interventions. Therefore, studying predictors of each intervention’s effect potentially enables us to determine who benefits most from what treatment – group-based or internet-based MBCT. In this study we would like to explore two possible predictors: the presence/absence of a DSM-IV-TR mood/anxiety disorder and the personality trait neuroticism.

Research on mindfulness-based interventions for cancer patients has focused on the prevalence and treatment of distress rather than psychiatric disorders. Not much is known on the effectiveness of MBCT in oncology patients suffering from a mood and/or anxiety disorder as opposed to patients suffering from distress. We are interested to see if the presence of a psychiatric disorder is a better predictor of treatment outcome than psychological distress.

Moreover, previous research has shown that a high score on neuroticism has a negative effect on (group) psychotherapy outcome (Ogrodniczuk et al. 2003). This study aims to explore the hypothesis that higher neuroticism at baseline has a negative predictive value for the primary outcome measure and to explore possible differences in treatment outcome between group- and internet-based MBCT.

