As it is known that mindfulness skills mediate the relationship between mindfulness practice and improvements in psychological symptoms (e.g. Gu et al. 2015), we hypothesize that the improvement on the Hospital Anxiety and Depression Scale (HADS) in the MBCT intervention arms is mediated by mindfulness skills. Moreover, weekly measurements (MAAS and I-PANAS-SF) will be used to test the hypothesis that an increase in mindfulness skills antedates changes in affect during the intervention.

One of the differences between face-to-face and online treatment is the relationship with the therapist. Working alliance, or therapeutic alliance, is a long-recognized concept in psychotherapy research. Although it is known that a working alliance is realizable in internet-based therapy (Cook and Doyle 2002), little is known about the possible difference in working alliance between group- and internet-based MBCT. We would be interested to see if working alliance mediates the relationship between intervention and outcome in both interventions.

The relationship with both the therapist and other group members in group-based treatment, or group cohesion, is often considered to be one of the most important contributors to positive treatment effect in group therapy. The current study aims to assess whether group cohesion mediates the relationship between the group-based MBCT intervention and outcome.

In conclusion, the primary aim of this study is to compare the effectiveness of group- and internet-based MBCT to TAU to reduce distress in cancer patients after treatment. Secondary outcome measures will be fear of cancer recurrence, rumination, and positive mental health. In addition, possible effect predictors (DSM-IV-TR mood/anxiety disorder and neuroticism) and mediators (mindfulness skills, working alliance, group cohesion) of treatment outcome will be explored. In order to determine the long-term stability of intervention effects, assessments will take place 3 and 9 months post-treatment. Alongside the clinical trial, the cost-effectiveness of both MBCT interventions compared to TAU will be determined. As far as we know, this is the first direct comparison between group-based MBCT, internet-based MBCT and TAU.

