## Primary outcome measure

For a measurement scheme we refer to Table 2. The primary outcome measure is the post-treatment total score on the HADS, a 14-item self-report screening scale that was originally developed to indicate the possible presence of anxiety and depressive states in the setting of a medical outpatient clinic (Zigmond and Snaith 1983; Spinhoven et al. 1997). As earlier research in a palliative setting suggested the total HADS score should be used, this score will be used rather than individual depression and anxiety subscales (Le Fevre et al. 1999). The HADS shows good psychometric properties in the general medical population, including oncology patients in palliative phase (Akechi et al. 2006). Internal consistency as measured with Cronbach’s α varied from .84 to .90 (Spinhoven et al. 1997; Bjelland et al. 2002). Test-retest reliability was good as Pearson’s r > .80 were obtained (Spinhoven et al. 1997; Herrmann 1997).

**Table 2 Tab2:** Measurement scheme

Variable goal	Measure	Target	Screening	T0	During	T0b (TAU only)	T1	T2	T3
Primary outcome	HADS	Psychological distress	x	x		x	x	x	x
Secondary outcomes	FCRI	Fear of cancer recurrence		x		x	x	x	x
	RRQ	Rumination Reflection Questionnaire		x		x	x	x	x
	MHC-SF	Mental Health Continuum – Short Form		x		x	x	x	x
Effect predictors	SCID	DSM-IV Axis I disorders		x		x	x	x	x
	NEO-FFI	Personality dimensions		x					x
Process measures	FFMQ-SF	Mindfulness skills		x		x	x	x	x
	WAI	Working alliance			x				
	GCQ	Group cohesion			x				
	MAAS	Mindfulness skills			x				
	I-PANAS-SF	Mood			x				
	Calendar	Mindfulness adherence			x				
Cost-effectiveness	TiC-P	Health care costs and productivity		x		x	x	x	x
	EQ-5D	Health-related quality of life (preference-based)		x		x	x	x	x
	SF-12	Health-related quality of life (general health profile)		x		x	x	x	x

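### The mediation model leaves T0 neuroticism out of the non-randomised mediator-to-HADS path; adding it is a cheap, minor improvement to an exploratory analysis

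*Protocol article*

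**What the plan says.** The Statistical analysis section sets two rules for every mediation model. For the outcome: "In all mediation analyses, post-treatment HADS scores are controlled for baseline HADS scores". For the mediators: "Residual change scores for all potential mediators are calculated". Confidence limits come from a bias-corrected and accelerated bootstrap. No further covariate is named.

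Three other places bear on neuroticism:

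- Process measures describes the FFMQ-SF as "inversely related to measures of psychological symptoms, experiential avoidance, and neuroticism".
- Background reports that "previous research has shown that a high score on neuroticism has a negative effect on (group) psychotherapy outcome" and sets out to explore whether "higher neuroticism at baseline has a negative predictive value for the primary outcome measure".
- Table 2, under Primary outcome measure, lists the NEO-FFI (target: "Personality dimensions") among the effect predictors, with marks that read as T0 and T3. It is therefore available before randomisation.

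The mediation hypothesis, in Background, is that the "improvement on the Hospital Anxiety and Depression Scale (HADS) in the MBCT intervention arms is mediated by mindfulness skills". Neuroticism is given a role as an effect predictor. Nothing places it in the mediation model.

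**The concern.** An indirect effect is the product of two paths. Randomisation protects the path from condition to mediator. The path from mediator to post-treatment HADS is a comparison of patients who gained more skill with patients who gained less, and so is observational. A trait that raises mindfulness gains and also lowers later distress makes that path non-zero even if the mediator does nothing. The bootstrap deals with sampling error, not with this bias.

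Neuroticism is the obvious candidate, because the article itself discusses it in relation to both the mediator and the outcome and measures it at baseline. At stake is the reading of mechanism: a positive result would be taken as evidence that MBCT works by teaching mindfulness skills. The problem is separate from the order in which mediator and outcome are measured, and would remain if that timing were changed.

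**Working it through.** The article states no figure to reproduce, so the check has two parts: what the text supports, and how large the bias could be under stated assumptions.

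**What the text supports.** Residualising FFMQ-SF on its own baseline removes the part of neuroticism carried by the baseline level. Bias then needs two further links: neuroticism predicting *change* in FFMQ-SF, and neuroticism predicting post-treatment HADS beyond baseline HADS. The first is not stated anywhere; the Process measures section reports an association with the level of the score only. The second is a hypothesis of this trial, with one cited study of psychotherapy outcome behind it.

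**Large-sample bias.** All inputs are assumed. Neuroticism N, baseline mediator M0 and baseline HADS Y0 are standardised, with corr(N, M0) = -0.5 and corr(N, Y0) = +0.5. M0 and Y0 are linked only through N, so corr(M0, Y0) = -0.25. T is condition, and the true mediator effect is zero.

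- M1 = 0.6 M0 + 0.5 T - g N + error (SD 0.7)
- Y1 = 0.5 Y0 - 0.5 T + h N + error (SD 0.8)

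After M1 is residualised on M0, what remains of N is N' = N + 0.5 M0. It has variance 0.75, covariance 0.75 with N, and covariance 0.5 + 0.5 x (-0.25) = 0.375 with Y0. Conditioning also on T and Y0, the residual change score has:

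- covariance with N: -g (0.75 - 0.375 x 0.5) = -0.5625 g
- variance: 0.49 + g^2 (0.75 - 0.375^2) = 0.49 + 0.6094 g^2

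The false mediator coefficient is therefore b = -0.5625 g h / (0.49 + 0.6094 g^2). The false indirect effect is 0.5 b. As a share of the total effect of -0.5 it equals |b|.

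| g = h | b | indirect effect | share of total | share in simulation (N = 400,000) |
|---|---|---|---|---|
| 0.1 | -0.005625 / 0.4961 = -0.011 | -0.006 | 1.1% | 1.0% |
| 0.2 | -0.0225 / 0.5144 = -0.044 | -0.022 | 4.4% | 4.5% |
| 0.3 | -0.050625 / 0.5448 = -0.093 | -0.046 | 9.3% | 9.2% |

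If g = 0 or h = 0 the bias is zero. With T0 neuroticism added to the outcome model, the simulated b was within 0.004 of zero in every scenario.

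**In HADS points.** At g = h = 0.3 the within-arm variance of Y1 is 0.25 + 0.09 + 2 x 0.5 x 0.3 x 0.5 + 0.64 = 1.13, an SD of 1.06. The false indirect effect is then 0.046 / 1.06, about 0.04 SD. With the SDs in the Sample size section this is 0.04 x 6.4 = 0.26 to 0.04 x 8.1 = 0.32 points. The planned difference is 14.8 - 10.6 = 4.2.

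**False mediation claims at trial size.** Simulations used n = 130 (2 x 65) and n = 195 (3 x 65), no true mediator effect, and joint significance of both paths at 5%. The figures below come from the main run of 4,000 replications.

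| g = h | stated model, n = 130 | stated model, n = 195 | adjusted, n = 130 | adjusted, n = 195 |
|---|---|---|---|---|
| 0.1 | 4.2% | 5.3% | 4.2% | 5.3% |
| 0.2 | 5.9% | 7.8% | 4.4% | 5.2% |
| 0.3 | 12.3% | 19.0% | 5.0% | 5.8% |

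Adjusted means that N and M0 are added to both equations. An independent run of 3,000 replications gave 4.8/6.1/10.8% (n = 130) and 4.3/6.5/15.9% (n = 195) for the stated model. A further run with other assumed inputs (autocorrelations 0.5 and 0.6) gave 6-9% at 0.2 and 16-37% at 0.3, so the figure at 0.3 is sensitive to values the article does not give. With neuroticism tied only to baseline levels the rate was 4-5%.

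**The case against.** The strongest reply is that the text shows no error. A reader might infer that the model adjusts for baseline HADS and nothing else. It does not: the next sentence takes out each mediator's own baseline, and with it the level association that the article reports. A reader might also infer that the article itself identifies neuroticism as a common cause of mediator change and HADS. It does not go that far, for the reasons given in the check. With level associations alone the stated model holds its nominal rate. These two replies stand, and they limit the point to a conditional one.

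It is also tempting to extend the point to working alliance and group cohesion. "The WAI is administered before session 2, 5 and 9", group cohesion follows the same schedule, and neither has a T0 value, so no pre-treatment residual change score can be formed for them. Under assumed effects of 0.3 on both paths, a mediator without a baseline gave false claims of 12-26%, against about 5% after adjustment. But the article describes no relation between either measure and neuroticism, so this extension is a precaution and not a documented flaw.

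A journal article may leave further covariates to a full analysis plan, and this one does not exclude them. That lowers the weight of the point without removing it, because the article does fix a control set for all mediation analyses and gives no sign of a longer one. The simulations also test joint significance, not the planned bootstrap, so the rates are indicative only. Finally, Background says the mediators will be explored, and any single-trial mediation analysis keeps some unmeasured confounding.

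**Conclusion.** The point holds in a limited form. The stated model leaves the mindfulness-to-HADS path open to confounding by a baseline trait that the article discusses on both sides and already measures. Whether there is bias depends on neuroticism predicting change in FFMQ-SF and also post-treatment HADS beyond its baseline; the first is assumed here and the second is only hypothesised in the article. On those assumptions the effect is negligible at 0.1, slight at 0.2, and clear only at about 0.3 on both paths. Even there the spurious effect is about 0.3 HADS points, or up to about 9% of the total effect. This is a minor improvement to an exploratory analysis. The superiority comparison with TAU is untouched.

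**What to change.** For mindfulness skills, add T0 neuroticism and the baseline FFMQ-SF score to both the mediator equation and the outcome equation, alongside condition and baseline HADS. For working alliance and group cohesion, add T0 neuroticism as a precaution, and state that no pre-treatment score exists. Report a sensitivity analysis showing how large a residual correlation between mediator and outcome would have to be to bring the indirect effect to zero.

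The cost is a change of analysis wording and a few degrees of freedom. No new measurement is needed, since the NEO-FFI and FFMQ-SF are both scheduled at T0. Adjustment for neuroticism reduces confounding of this path but cannot rule it out, which is why the sensitivity analysis belongs with it.
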